## Methods and analysis

2.

### Study design

2.1.

The present study is a two-arm, parallel randomized controlled trial with an intervention group compared to a control group receiving treatment as usual. The intervention group receives a three-week online-based intervention guided by the chatbot ELME. The control group receives no content and just answers the questionnaires and the ecological momentary assessments. Treatment as usual for the control group was chosen based on methodological recommendations for randomized controlled trials and psychological interventions (71, 78, 79). Primary and secondary outcomes will be assessed in both groups at screening (t0), pre-intervention (t1), daily during the intervention (between t1 and t2), post-intervention (t2), as well as follow-up three weeks after t2 (t3). The study will be conducted in accordance with the Consolidated Standards of Reporting Trials (CONSORT) 2010 Guidelines for Randomized Controlled Trials (71, 73). The study protocol corresponds the recommendations of the “Standard Protocol Items: Recommendations for Interventional Trials” checklist for clinical trial protocols (SPIRIT; 80).

### Eligibility criteria

2.2.

Participants will be included in the present study if they (a) are 18 years or older, (b) have sufficient knowledge of the German language, (c) own a smartphone (Android or iOS) with internet access, (d) possess a valid German phone number, (e) possess a valid mail address, (f) experience middle to high perceived stress (PSS-10 score ≥ 14, assessed at t0), (g) are not diagnosed with any mental disorder, (h) do not currently undertake psychotherapy, and (i) do not currently participate in another mental health online-intervention.

### Setting and recruitment

2.3.

Recruitment of the study has started in February 2022 and will be continued until the targeted sample size of *N *= 130 has been reached. Recruitment takes place online and offline targeting German speaking people. Offline recruitment strategies comprise flyers and posters at different public places such as universities, fitness centers, educational institutions, corporate health management, psychosocial counselling services, and city libraries in Germany. Online recruitment will be implemented *via* e-mail distribution lists, e.g., in the area of occupational health management, universities, postings on social media (e.g., LinkedIn), online self-help groups on social media. Apart from the possibility to take part in a chatbot-based intervention for free, participants receive the chance to win a € 25 gift card from an online shop or, as a student participant, to receive 5 course credits as expense allowance for completing the questionnaires. Furthermore, both intervention and control participants receive the option to get access to two relaxing exercises and to get individual summaries regarding the change in their health-related parameters in the course of t1 to t3 after completing the t3 questionnaire.

### Study procedure

2.4.

Interested individuals can access to the screening questionnaire (t0) *via* the landing page, after they have registered with their mail address and their phone number and verified those. The landing page can be reached *via* a link or a QR code. If participants fulfill the inclusion criteria (see Figure 1), they will be forwarded to the pre-intervention questionnaire (t1). As the first part of the t1 questionnaire, participants obtain and have to agree with the informed consent of the study. The questionnaires t0-t3 take place *via* the online survey tool Unipark (https://www.unipark.com). After completing the t1 questionnaire, included participants will automatically receive an SMS with a personalized link to the specifically developed chatbot platform. By linking the participants' sessions to their mobile numbers, the phone is used as the sole authentication factor and no other credentials are required for personalized access. Apart from offline recruitment strategies, the study will be fully conducted online. Excluded participants are informed that they could not take part in the study and receive alternative contact institutions such as psychosocial contact institutions or platforms to find psychotherapists. Ecological momentary assessments take place *via* the chatbot platform. Figure 1 represents the planned study procedure. A participant timeline for the intervention and the control group is depicted in Figure 2.

**Figure 1 F1:**
[figure not shown]
Flow chart of the planned study procedure.

**Figure 2 F2:**
[figure not shown]
Participant timeline for the intervention and the control group. *EMA,* Ecological momentary assessment.

### Randomisation and blinding

2.5.

After completing the t1 questionnaire, the platform automatically assigns participants randomly to the intervention group or to the control group. The assignment is based on a platform-internal pseudorandom number generator with an allocation ratio of 1:1. Data analyses are performed with pseudonymous data, where the analysts do not learn about the participants' identities. Primary and secondary outcome analysis are performed with a blinded data set, which conceals the group allocation while keeping all participants of the same group in the same blinded group.

### Intervention

2.6.

ELME is a rule-based, conversational chatbot and was developed by members of the Department of Clinical and Health Psychology and the Institute of Distributed Systems at Ulm University. This type of technology is a self-developed, web-based chatbot platform, provided *via* smartphone with SMS notifications. The input modality is written; the output modality is also written, except audio files provided by the chatbot.

The chatbot-based intervention aims at stress reduction and improving health-related parameters such as interoception and mindfulness. In particular, the intervention contents mainly address the constructs of stress, interoception and mindfulness as well as their association, provided *via* psychoeducation and exercises (e.g., audio files such as breathing exercises) in a real-time dialogue with the chatbot. The intervention units are offered twice a day with one session in the morning and one session in the afternoon or evening over the course of three weeks, depending on the self-selected time of a participant. The times of the units could be switched daily *via* a settings menu in the chatbot platform. In the weekends, only one session takes place, the day can be freely selected by each participant. Importantly, the contents and exercises aim to be closely related to everyday life. Therefore, the chatbot asks questions related to current situations of the participants and exercises are designed short (10–20 min). The gender-neutral persona of the chatbot is characterized by a friendly demeanor as an empathetic companion with expertise in mental health. ELME's communication style can be described as calm, tolerant, supportive, and appreciative. For each start of a session with ELME, the participant receives an SMS. Furthermore, participants receive reminder SMS to fulfill the units with ELME and they could postpone single exercises to one hour later. Participants have to complete each session within three hours; otherwise ELME aborts the session automatically to assure the course of upcoming sessions. Moreover, the chatbot platform menu provides answers to frequently asked questions, a download function for the audio files and summaries of the single exercises.

The contents are based on approaches of mindfulness-based stress reduction (81–83), stress management (84, 85), Acceptance and Commitment Therapy (86, 87), heartbeat perception exercises derived from the heartbeat tracking task (88), and psychoeducative elements of a guided online mindfulness-based intervention called “StudiCare Mindfulness” (32). An overview of the alternating intervention contents representing the modules “stress”, “interoception”, “mindfulness” or the “association of stress, interoception, and mindfulness” is shown in Table 1. In every training session, ELME introduces the participants to a main topic by psychoeducation, provides everyday examples and corresponding exercises. Aiming to make the participants integrate the topics into their everyday life, central intervention contents and exercises are repeated. They are engaged in the interaction with ELME by answering questions with pre-defined response alternatives, on a numeric slider or *via* an open text. Based on a fixed set of rules, the communication logic is implemented as a finite-state machine. On each incoming message sent by the participant, ELME responds with an appropriate answer. ELME purposefully and frequently involves users in the conversation to ensure their active participation, also reminding of responding by diverse text phrases. A sample dialogue of the chatbot interacting with a participant is depicted in Figure 3 (in German language).

**Figure 3 F3:**
[figure not shown]
Sample dialogue of the chatbot interacting with a participant.

**Table 1 T1:** Overview of the intervention contents.

Module	Aims and content	Presentation form
Stress		
Introduction into the construct stress	Psychoeducation; understanding the benefit of the intervention	Chat dialogue
Stress Traffic Light	Instruction of the Stress Traffic Light (84), training of stress perception and management	Chat dialogue
Stress reliever	Psychoeducation and reflection of stress relieving methods	Chat dialogue
Theory unit regarding stress	Impulses targeting stress management, coping strategies	Chat dialogue
Interoception		
Introduction into the construct interoception	Psychoeducation (e.g., 15, 89) understanding the benefit of the intervention	Chat dialogue
Heartbeat tracking task in sitting and lying position; walking	Exercise targeting interoception / heartbeat perception; adaption to the heartbeat tracking task (88, 27, 90)	Chat dialogue, audio file
Mindfulness		
Introduction into the construct mindfulness	Psychoeducation (e.g., 8) understanding the benefit of the intervention	Chat dialogue
Query of the most (non-)mindful moment of the day	Mindfulness exercise in every-day life, reflection	Chat dialogue
Body Scan	Mindfulness exercise	Audio file
Mindful drinking of water	Mindfulness exercise/Perception of satiety/pleasure	Chat dialogue
Mindful walk	Mindfulness and relaxation exercise	Chat dialogue
Association of stress, interoception & mindfulness		
Breathing exercise	Stress reduction and mindfulness exercise	Audio file
Query of satiety	Exercise targeting interoception/mindful perception of satiety	Chat dialogue
Association of stress, interoception and mindfulness	Psychoeducation, e.g. by explaining empirical findings (20, 18, 17, 91)	Chat dialogue
Free sports activity	Health promotion by physical activity as a positive impact on interoception, mindfulness and stress reduction (91)	Chat dialogue
Final summary	Reflection of the whole intervention, repetition	Chat dialogue, PDF file for downloading
Bouquet of flowers	Summary and explanation of all intervention exercises	PDF file

### Treatment as usual control group

2.7.

The control group receives no treatment. Participants of the control group only do the assessments, i.e., the questionnaires t0–t3 and daily ecological momentary assessments.

### Outcome assessment

2.8.

#### Primary outcome: stress

2.8.1.

To screen the participants concerning their acute perceived stress levels as an inclusion criterion, the 10-item version Perceived Stress Scale (PSS-10; 92) is used. Acute perceived stress regarding the last month is rated as the degree to which situations in one's life are rated as stressful on a scale ranging from 0 = “never” to 4 = “very often”. Within the questionnaires from t1 to t3, the 4-item short scale (PSS-4) is implemented. The ratings on both scales are quantified as sum scores with higher scores representing higher perceived stress. The German version of the PSS-10 demonstrated good internal consistency (Cronbach's Alpha = .84; 93) and the PSS-4 exhibited acceptable and reliable psychometric properties across cultures (Cronbach's Alpha = 0.77, 94).

#### Secondary outcomes

2.8.2.

##### Self-reported interoceptive accuracy

2.8.2.1.

Interoception, specifically, self-reported interoceptive accuracy, will be assessed *via* German versions of the Interoceptive Accuracy Scale (IAS; 95) and the subscale “Awareness” of the Body Perception Questionnaire (BPQ; 96). A self-translated German version of the IAS is used. The IAS consists of 21 items asking the participants how well they believe they can perceive specific bodily sensations on a 5-point Likert scale ranging from 1 = “disagree strongly” to 5 = “strongly agree”. Based on calculated sum scores (range: 21–105), higher scores reflect greater self-reported interoceptive accuracy. The internal consistency of the IAS is high with Cronbach's Alpha of 0.88 (95, 97). The BPQ comprises 45 items describing body processes which should be rated concerning the awareness during most situations on a 5-point Likert scale ranging from 1 = “never” to 5 = “always”. A mean score of the subscale “Awareness” is calculated. Based on a mean of 50 and a standard deviation of 10, t scores represent standardized values according to a normal distribution. High internal consistency with Cronbach's Alpha of 0.92 (98) and 0.97 (97) was shown.

##### Ecological momentary assessment

2.8.2.2.

Ecological momentary assessment includes questions on acute perceived stress, body awareness, interoception, and mood in the according moment. Participants have to answer the questions on a visual analogue scale based on horizontal rating sliders ranging from 0 “ = not at all” to 100 = “very much”. Comparably to the ecological momentary assessment in a previous study (99), acute perceived stress is assessed *via* two adapted items for the momentary use of the Perceived Stress Scale Short form (PSS-4; 92): “Do you feel that things are going your way?” and “Do you find you can cope with all the things that you have to do?”. Furthermore, two items addressed the body awareness: “How present do you feel at the moment?” and “How aware are you of your own body at the moment?” (27, 90). To assess self-reported interoceptive accuracy, we developed a question, which takes the heartbeat perception task by Schandry (88) into account: “How intense do you perceive your heartbeat in the moment?”. Based on previous studies (e.g., 99, 100), questions regarding mood comprise six positive emotions (cheerful, enthusiastic, awake, active, relaxed, calm) and five negative emotions (irritated, bored, nervous / stressed, worried, depressed), also assessed *via* a visual analogue scale ranging from 0 = “not at all” to 100 = “very much”.

##### Mindfulness

2.8.2.3.

Mindfulness is assessed *via* the 14-item short version of the Freiburg Mindfulness Inventory (FMI; 101). The FMI consists of a 4-point Likert scale ranging from 1 = “rarely” to 4 = “almost always” which are added to a sum score (range: 14–56). Higher scores indicate higher mindfulness. High internal consistency (Cronbach's Alpha = 0.84; 102) and sensitivity to change (101) were demonstrated.

##### General anxiety

2.8.2.4.

The 7-item Generalized Anxiety Disorder Questionnaire (GAD-7; 103) is used to screen for generalized anxiety disorders. Anxiety symptoms regarding the last two weeks are rated on a 4-point Likert scale ranging from 0 = “not at all” to 3 = “nearly every day”. A sum score (range: 0–21) is calculated. The GAD-7 has been proven as a reliable and valid measurement instrument of anxiety in the general population (Cronbach's Alpha = 0.89; 104). Furthermore, (103) reported a sensitivity of 0.89, a specificity of 0.82 and a good test-retest reliability (intraclass correlation = 0.83).

##### Depression

2.8.2.5.

The Patient Health Questionnaire (PHQ-8; 105) is an 8-item version of the reliable and valid PHQ-9 (106) without the ninth item requesting suicidal or self-injurious thoughts. The questionnaire assesses depressive symptoms within the last two weeks prior to measurement. Leaving out the ninth item might be more applicable in the context of an online- and smartphone-based study, as the handling with participants exhibiting suicidal or self-injurious thoughts without personal contact might be not adequate (105). A sum score (range: 0–24) is calculated from the ratings on a 4-point-Likert scale ranging from 0 = “not at all” to 3 = “nearly every day”. Based on a cutoff score of 10, the PHQ-8 showed a sensitivity of 0.86 (95% CI = 0.80–0.90) and a specificity of 0.86 (95% CI = 0.83–0.89; 107).

##### Personality

2.8.2.6.

The short version of the Big Five Inventory (108, 109) is used to measure the Big Five personality dimensions with two items per dimension. The 5-point Likert scale ranges from 1 = “fully disagree” to 5 = “fully agree”, which are calculated to a mean score. The questionnaire exhibited sufficient psychometric properties with an average retest reliability of 0.56.

##### Emotion regulation

2.8.2.7.

Emotion regulation is assessed *via* the German version (110) of the Emotion Regulation Questionnaire (111). The questionnaire comprises 10 items representing the two different emotion regulation strategies reappraisal (6 items) and suppression (4 items). Participants are instructed to rate the items on a scale ranging from 1 = “strongly disagree” to 7 = “strongly agree”. A higher mean for one of the two subscales reflects the preference for the respective strategy. Good internal consistencies were found for both subscales suppression (Cronbach's Alpha = 0.76) and for reappraisal (Cronbach's Alpha = 0.74; 110).

##### Psychological well-being

2.8.2.8.

The well-established 5-item WHO Well-Being Index (WHO-5; 112, 113) is utilized to assess subjective psychological well-being, in particular, the frequency of respective feelings over the last two weeks. Participants are instructed to response on a 5-point Likert scale ranging from 5 = “all of the time” to 0 = “at no time”. To calculate the total score, the sum score is calculated from raw scores (range: 0–25) and then multiplied with 4 (range: 0–100; 100 = best well-being). Based on several clinical studies, the WHO-5 demonstrated a sensitivity of 0.86 and a specificity of 0.81 as a screening tool for depression (113). A recent study (114) reported a Cronbach's Alpha of 0.75.

##### Stress mindset

2.8.2.9.

The Stress Mindset Measure (SMM; 76) is used to assess the individual general mindset if the effects of stress are enhancing or debilitating. The questionnaire consists of 8 items which the participants rate on a 5-point Likert Scale ranging from 0 = “strongly disagree” to 4 = “strongly agree”. Three optional preliminary questions address the current amount of stress (1 = “none”, 7 = “an extreme amount”), the primary source of stress in the individual's life and as how stressful this is perceived (1 = “not stressful”, 7 = “extremely stressful”). SMM scores are computed by means including the reverse scoring of four negative items. Higher scores indicate the mindset that stress is enhancing. The questionnaire demonstrated good internal consistency with Cronbach's Alpha = 0.86, which is similar for the German version (76, 115).

##### Treatment expectancy

2.8.2.10.

Treatment expectancy regarding the intervention is measured by the Credibility Expectancy Questionnaire (116), adapted for the chatbot-based intervention. Prior to randomisation, participants of the intervention as well as of the control group rate four items on a 9-point Likert scale and two items on a 10-point Likert scale. The scale reflects the two factors “credibility” and “expectancy”. Higher mean scores represent positive credibility and expectations. Cronbach's Alpha of 0.84 to 0.85 for the total scale indicated high internal consistency (117).

##### Affinity for technology

2.8.2.11.

The affinity for technology as an interaction style with technical systems, based on the established psychological construct need for cognition, was assessed *via* the Affinity for Technology (ATI) Scale (118). In this context, “technical systems” refer to apps, software applications or digital devices, respectively, the chatbot-based platform in the present study. Nine items are rated on a Likert scale ranging from 1 = “completely disagree” to 6 = “completely agree” and are calculated to an overall mean score. Based on multiple studies, the ATI Scale exhibited good psychometric properties regarding reliability (Cronbach's Alpha between .83 and .92), validity, dimensionality and distribution of ATI score values (118).

##### Attitude towards artificial intelligence

2.8.2.12.

The attitude towards artificial intelligence is assessed *via* the 5-item Attitude Towards Artificial Intelligence (ATAI) Scale (119). The according 11-point Likert scale ranges from 0 = “strongly disagree” to 10 = “strongly agree”. The ATAI Scale comprises the two factors “acceptance” and “fear”. A total mean score is calculated based on the means of the two subscales. In a study with a German sample (119), internal consistency for the subscale “acceptance” of artificial intelligence was at Cronbach's Alpha = 0.65 and for “fear” of artificial intelligence at Cronbach's Alpha = 0.66.

##### Satisfaction with the intervention

2.8.2.13.

To assess the global satisfaction with the intervention, a German version of the Client Satisfaction Questionnaire (CSQ-8; 120) adapted for the evaluation of internet-based interventions (121) was used. The CSQ-8 comprises eight items with diverse 4-point rating scales regarding the satisfaction such as 1 = “No, definitely not”, 4 = “Yes, definitely”, or 1 = “quite dissatisfied”, 4 = “very satisfied”. A sum score is computed with higher scores indicating higher satisfaction. Internal consistency of the CSQ-8 has been identified as high with Cronbach's Alpha between 0.88 and 0.92 (120, 122). In a study based on two randomised control trials investigating web-based interventions, results showed a good overall psychometric quality of the CSQ-8 (121).

##### Mental health app usability questionnaire

2.8.2.14.

The 18-item Mental Health App Usability Questionnaire (MAUQ; 75) is used to measure the usability of the chatbot as a mental health App, consisting of the three subscales „ease of use“ (5 items), „interface and satisfaction“ (7 items) and „usefulness“ (6 items). The rating scale ranges from 1 = “strongly agree” to 7 = “strongly disagree”. Mean scores for each subscale and a total mean score are calculated. The lower the mean score, the higher the usability. For the present study, a self-translated German translation of the MAUQ is used. The MAUQ exhibited an excellent internal consistency (Cronbach's Alpha = 0.91, 75).

##### Negative effects

2.8.2.15.

The Inventory for the Assessment of Negative Effects of Psychotherapy (INEP; 123) assesses potential negative effects of psychotherapy (e.g., intrapersonal change, relationships, or stigmatization). The scale comprises 21 items, including four items which are rated on a 7-point bipolar scale (−3 = “worse; + 3 = “better”), calculated to mean scores with lower values reflecting more negative effects. The other items are rated on a 4-point Likert scale ranging from 0 = “not at all” to 3 = “totally agree”. In the present study, an 18-item version adapted to possible negative effects of the chatbot-based intervention (e.g., excluding items regarding the therapist) is used to assess potential negative effects of the chatbot-based intervention. The original questionnaire exhibited a high internal consistency with a Cronbach's Alpha of 0.86 (123).

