##### Adherence

2.8.2.16.

According to the suggested guidelines regarding adherence in randomised controlled trials investigating online interventions (124), adherence to the intervention is operationalized by the percentage of completed intervention units. All assessed variables, the according measurement instruments and measurement points are depicted in Table 2. Reasons for potential dropout reasons are assessed *via* the Dropout Reasons Questionnaire for Internet Interventions (125).

**Table 2 T2:** Assessed variables, measurement instruments and measurement points.

Variables	Measurement instrument	Measurement point				
		T0	T1	T1–T2	T2	T3
Primary outcome						
Acute perceived stress	Perceived Stress Scale (PSS-10)	X				
Acute perceived stress	Perceived Stress Scale - short form (PSS-4); 2 items (EMA)		X	X	X	X
Secondary outcomes						
Demographic variables (e.g., age, gender, pre-experience with chatbots)	Demographic Questionnaire		X			
Self-reported interoceptive accuracy	Interoceptive Accuracy Scale		X		X	X
Self-reported interoceptive accuracy	Awareness Scale of the Body Perception Questionnaire		X		X	X
Self-reported interoceptive accuracy	Interoceptive item (EMA)			X		
Body Awareness	Body awareness items (EMA)			X		
Mood	Visual Analogue Mood Scale (EMA)			X		
Mindfulness	Freiburg Mindfulness Inventory – short form (FMI)		X		X	X
General anxiety	General Anxiety Disorder (GAD-7)		X		X	X
Depression	Patient Health Questionnaire (PHQ-8)		X		X	X
Personality	Big Five Inventory (BFI-10)		X			
Emotion regulation	Emotion Regulation Questionnaire (ERQ)		X		X	X
Psychological well-being	WHO-5 Well-Being Index		X		X	X
Stress mindset	Stress Mindset Measure (SMM)		X		X	X
Intervention credibility and expectancies	Credibility / Expectancy Questionnaire (CEQ)		X			
Affinity for Technology	Affinity for Technology Interaction (ATI)		X			
Attitudes towards Artificial Intelligence	Attitudes towards Artificial Intelligence (ATAI) Scale		X		X	X
Satisfaction with the intervention	Client Satisfaction Questionnaire (CSQ-8)				X	
Usability of the app	Mental Health App Usability Questionnaire (MAUQ)				X	
Negative effects of the intervention	Inventory for the assessment of Negative Effects of Psychotherapy (INEP)				X	X
Adherence	Percentage of completed intervention units				X	
Dropout reasons	Dropout Questionnaire				X	
Open feedback questions regarding the chatbot					X	

Notes. EMA, ecological momentary assessment.

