### Sample size estimation

2.9.

The sample size was calculated by an a-priori power analysis for a repeated measurement ANOVA *via* G*Power (126), comparing two groups. Assuming a small effect size of *f* = 0.15 (consistent with *d* = 0.30), based on an *α*-level of 0.05, a power of 0.90, and a dropout rate of 40%, the sample size analysis resulted in *N* = 130 participants (*n* = 65 in the intervention group, *n* = 65 in the control group). As previous findings regarding chatbot-based interventions in the area of mental health are sparse, the assumed effect size of *d* = 0.3 was determined based on a systematic review (127), reporting effect sizes of *d* = 0.29 for depression and *d *= 0.15 for anxiety. A review and meta-analysis based on online mindfulness-based interventions stated small effect sizes for mindfulness (*g* = 0.32), depression (*g* = 0.29), anxiety (*g* = 0.22), and well-being (*g* = 0.23). It needs to be noted that results regarding adherence, respectively, attrition rates in online or chatbot-based interventions are also sparse or often not reported (124, 55). The dropout rate of 40% is estimated based on the systematic review of adherence to web-based interventions (128) and the adherence rates of guided interventions (39, 45, 46).

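### Mean scores on the four worse-to-better INEP items measure net change, so improvement can offset deterioration; counts of participants with ratings below 0 should be reported alongside

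*Protocol article*

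**What the plan says.** Section 2.8.2.15 (Negative effects) introduces the INEP as the measure of potential negative effects. Of the original instrument it says "The scale comprises 21 items", "including four items which are rated on a 7-point bipolar scale", with -3 meaning worse and +3 meaning better. These four are "calculated to mean scores with lower values reflecting more negative effects". A separate sentence covers the rest: "The other items are rated on a 4-point Likert scale ranging from 0" (not at all) to 3 (totally agree). That sentence gives neither a scoring rule nor a direction.

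The trial uses "an 18-item version adapted to possible negative effects of the chatbot-based intervention". The section does not repeat the scoring for this version or say how many of the four bipolar items it keeps. Table 2 schedules the INEP at T2 and T3, and it is the only instrument there labelled for negative effects.

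**The concern.** The instrument is included to show whether the chatbot made things worse for anyone. The scoring rule stated for the bipolar items answers a different question, namely what the average change was. On a scale centred on no change, each better rating is added and each worse rating subtracted, so the mean cannot tell uniform mild benefit from a mixture of benefit and deterioration.

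Two errors of reading follow. A mean above 0 does not show that nobody deteriorated. A lower mean, which the article equates with more negative effects, may only mean that fewer people improved. For the same number of people worse, the offset grows with the benefit in the others, so the mean is least informative about harm if the intervention works as hypothesised. What is at stake is the trial's statement about harm on these items. The primary outcome, the sample size and the significance level are not affected.

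**Working it through.** The article states no result or target for the INEP, so there is no figure to reproduce. The check is direct arithmetic on the stated scale.

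**Inputs.** From section 2.8.2.15: four items, integer ratings from -3 to +3, scored by the mean. From section 2.9: 65 participants planned per arm, with 40% dropout allowed for. The ratings of -2 and +1 used below are assumptions for illustration; the article gives no expected ratings.

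**Netting across people.** If a share p rates -2 and the rest rate +1, the mean is p × (-2) + (1 - p) × 1 = 1 - 3p.

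| Share worse, p | Mean |
|---|---|
| 10% | +0.70 |
| 20% | +0.40 |
| 30% | +0.10 |
| 33.3% | 0.00 |

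In whole people at n = 65, 13 at -2 and 52 at +1 give (-26 + 52)/65 = +0.40. With 40% dropout, 65 × 0.60 = 39 remain; 8 at -2 and 31 at +1 give (-16 + 31)/39 = +0.38. More generally, if those affected rate -a and the others +b, the mean reaches 0 at p = b/(a + b). The crossing point depends on the assumed values, but the offset is there for any positive a and b.

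**A lower mean without harm.** If all 65 rate +1, the mean is +1.00. If 26 rate +1 and 39 rate 0, it is 26/65 = +0.40. The mean has fallen and nobody is worse. This is the same +0.40 as with 13 of 65 (20%) worse.

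**Netting within a person, if the four items are averaged together.** The pattern (-3, +1, +1, +1) has mean 0/4 = 0.00, the same as (0, 0, 0, 0). Over all 7^4 = 2401 possible patterns:

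- 4^4 = 256 contain no negative rating, so 2401 - 256 = 2145 contain at least one. By enumeration, 1060 of these (49.4%) still have a mean of 0 or more.
- 6^4 = 1296 contain no -3, so 2401 - 1296 = 1105 contain at least one. Of these, 330 (29.9%) have a mean of 0 or more.

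These are shares of possible patterns, not expected frequencies among participants.

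**The 0-to-3 items.** Their floor is 0, so no answer can cancel another and they cannot net benefit against harm. If all four bipolar items are kept (assumption), 18 - 4 = 14 of the 18 items are of this kind.

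**The case against.** A reader might infer something stronger: that the 0-to-3 items run the opposite way to the bipolar ones, so that harm could disappear from the INEP as a whole. That would need one unreversed total over both item types. With all four bipolar items at -3 and four of 14 others at 3, such a total would average (-12 + 12)/18 = 0.00. But the article describes no such total. The mean-score clause attaches to the four bipolar items, and the remaining items come in a separate sentence. Scored separately, the same person has -3.00 on the bipolar items and 12/14 = 0.86 on the others, so the harm stays visible. The opposite direction is itself only an inference from the anchors. This objection stands.

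A reader might also infer that a mean above 0 would be reported as no negative effects. The article sets no such threshold, so this is a risk of interpretation and not a stated rule.

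Three further objections stand in part:

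- The mean-score clause sits in the description of the original 21-item scale and does not settle whether the mean is per item or across items. The within-person result therefore depends on one reading. The across-person result holds on either.
- A condensed article may leave item-level counts to a fuller document, so their absence is not an error in itself. The point rests on the scoring rule that is stated.
- Worsening could also show in the GAD-7, PHQ-8 and WHO-5 at T1 to T3, or in dropout reasons and open feedback at T2. The three scales do not ask about effects attributed to the chatbot, and none of these sources is the dedicated measure.

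**Conclusion.** The point holds for the bipolar items only. As stated, their mean is net change: it can offset deterioration with improvement across participants, and within a participant if averaged across items, and a lower value need not mean harm. Under the assumed ratings, 20% of users worse by 2 points is compatible with a mean of +0.40, and the mean reaches 0 only when a third are worse. Those figures depend on the assumed -2 and +1; the offset itself does not.

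The documents do not support the conclusion that harm would vanish from the INEP overall, or that the 0-to-3 items mask it. This is a low-cost improvement to what the trial can say about harm on a secondary measure. It has no bearing on the primary analysis.

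**What to change.** Keep the means for the bipolar items. Alongside them, report the number and percentage of participants with a rating below 0, for each item and for any of the bipolar items, with exact 95% confidence intervals, at T2 and at T3. Say how many bipolar items the 18-item version retains and whether means are per item or across items. Score the 0-to-3 items separately and state which direction indicates more negative effects.

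The cost is one extra table from data already being collected. Counts are noisier than means, particularly with about 39 of 65 per arm left after the allowed dropout. An any-item count also treats one mild -1 the same as a -3 and could overstate harm, so the table should show the distribution of ratings from -3 to +3 for each item.
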